**Treatment Plan**:

- Sutent be administered PO QD from days 1 to 28 (see Figure 1)

Figure 1. Treatment Schema

Determine eligibility

**↓**

| **REGISTER** | **Treatment** | Days  1-7 | 8-12 | 13-14 | 15-19 | 20-28 | 29-42 |
| --- | --- | --- | --- | --- | --- | --- | --- |
| XRT |  | X |  | X |  |  |
| Sutent | X | X | X | X | X |  |

**↓**

Additional chemotherapy (as determined by Medical Oncology)

**↓**

Maintenance Sutent (until death or progression) and appropriate follow-up

- Radiation therapy will start on day 8 and will be given to each site for ten fractions
- Fractions must be separated by at least 16 hours
- The MTD of radiation in combination with Sutent will be determined
- Doses of radiation and Sutent will increase as shown in Table 1 in order to determine the MTD of radiation in Gy and Sutent in mg
- The RPTD will be one dose level lower than the MTD. If the MTD is not reached at dose level 5, no further escalation will occur and this will be the RPTD. The RPTD will then be used for future phase II trials.
- Starting day 43, chemotherapy may be given, as determined by the treating medical oncologist.
- Two weeks after completion of any chemotherapy, maintenance Sutent in 6 week cycles (consisting of Sutent 50 mg PO QD weeks 1-4 followed by no treatment weeks 5-6) until progression or death
- If no chemotherapy is planned, maintenance Sutent (as described above) will start on day 43.

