**Table 1. Phase I Dose Levels**

| **Dose Level** | **Radiation Dose** | **Sutent Dose** |
| --- | --- | --- |
| 1 | 40 Gy in 10 fractions | 25 mg PO QD |
| 2 | 40 Gy in 10 fractions | 37.5 mg PO QD |
| 3 | 50 Gy in 10 fractions | 37.5 mg PO QD |
| 4 | 50 Gy in 10 fractions | 50 mg PO QD |
| 5 | 60 Gy in 10 fractions | 50 mg PO QD |

.

Phase I dose escalation will proceed according to a “3+3” design. After 3 patients have been treated on each dose level, they will be followed for at least 30 days. If 0 of 3 patients have DLTs, the dose will be escalated to the next dose level. If ≥2 of 3 patients have DLTs, dose escalation will be terminated and the next lowest dose level will be declared the maximal tolerated dose for Phase II evaluation. If 1 of 3 patients has a DLT, then three more patients will be treated at the same dose level and if the incidence of DLT among six patients is < 2 of 6, the dose will be escalated to the next level for that site.

- Grades 3-5 non-hematological toxicities (excluding nausea, vomiting, and alopecia) and Grade 4-5 hematological toxicities will be referred to as dose limiting toxicities (DLT).
  - Esophagitis and mucositis are very common side effects with radiation therapy and grade 3 side effects can be seen after palliative courses of radiotherapy. Therefore, grade 3 mucositis or esophagitis lasting ≤ 7 days will **not** be considered a DLT. If the grade 3 mucositis or esophagitis lasts > 7 days, it will then be considered a DLT.
- The recommended phase II dose will be 1 dose level below the defined MTD or at the maximum tested dose if the MTD has not been reached.

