**16. STATISTICAL CONSIDERATIONS**

- Phase I: The primary objectives are to determine the maximum tolerated dose (MTD) and dose limiting toxicity (DLT) of extracranial stereotactic radiation therapy in combination with Sutent when given to all sites of involved disease in patients with metastatic cancer.
- For dose escalation purposes, the major endpoint will be dose-limiting toxicity occurring within 30 days after the start of radiation therapy.
- Dose limiting toxicity is defined as follows: Grade 3-5 non-hematological toxicities (excluding nausea, vomiting, and alopecia) and Grade 4-5 hematological toxicities.
  - Esophagitis and mucositis are very common side effects with radiation therapy and grade 3 side effects can be seen after palliative courses of radiotherapy. Therefore, grade 3 mucositis or esophagitis lasting ≤ 7 days will not be considered a DLT. If the grade 3 mucositis or esophagitis lasts > 7 days, it will then be considered a DLT.
- The MTD for a specific area will be exceeded if 2 or more patients out of 6 (or a third or more) with disease at that site experience DLT at that dose. The dose immediately below will be recommended for further study.
- Phase II: *(Includes 3 to 6 patients from Phase I MTD):* The median progression free survival with optimal chemotherapy alone for the 4 most common tumor types (lung, breast, prostate and colorectal) ranges from 2.2 to 10.6 months, depending on primary tumor site and degree of pretreatment. Therefore, we will assume a median time to progression of 6.4 months (standard deviation 3.2 months) with chemotherapy alone. With 38 patients, this study has 87% power (α=0.05) to detect a 25% increase in time to progression. Also the 2 year freedom from progression is <5% with chemotherapy therapy and this study has 70% power (α=0.05) to demonstrate a 10% absolute increase in 2 year progression-free survival.
  - All patients included in the study will be assessed for response to treatment, even if there are major protocol treatment deviations or if they are ineligible (intent-to-treat population). Criteria described in Section 10 will be used to assign each patient to one of the following response categories: 1) complete response, 2) partial response, 3) stable disease, 4) progressive disease, 5) early death from malignant disease, 6) early death from toxicity, 7) early death because of other cause, or 8) unknown (not assessable, insufficient data).

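### The phase II dose level can rest on 0 DLTs in 3 patients, and phase II has no numeric DLT proportion that sends accrual to the committee: a minor, cheap safeguard to add, not an error in the 3+3 rule

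*Protocol*

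**What the plan says.** **Phase I.** Under Section 10, three patients without a DLT clear a level. Three more are added only after 1 DLT in 3. With 2 or more, "dose escalation will be terminated and the next lowest dose level will be declared the maximal tolerated dose for Phase II evaluation". For the top level, the synopsis (Treatment Plan) says "If the MTD is not reached at dose level 5, no further escalation will occur and this will be the RPTD". Section 16 states the consequence openly for phase II: "Includes 3 to 6 patients from Phase I MTD". The event counted is "dose-limiting toxicity occurring within 30 days after the start of radiation therapy".

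**The DLT limit.** Section 16 puts it at 2 of 6 patients ("or a third or more) with disease at that site experience DLT at that dose"). It stands among the phase I bullets and is worded per site, as is Section 10 ("the dose will be escalated to the next level for that site"). No section carries it into phase II.

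**Phase II oversight.**
- Section 9.10 interrupts or lowers Sutent in the affected patient.
- Section 12 requires immediate reporting and evaluation of life-threatening grade 4 and all fatal toxicities.
- Section 15 provides biweekly toxicity review.
- Appendix 3 (Phase I/II and Phase II Trials) has regular meetings discuss, for each arm or dose level, how many patients were treated and what significant toxicities occurred.
- Appendix 3 (Quarterly Review) has the committee consider closure.
- Appendix 3 (Review of Adverse Event Rates) calls for a review by the committee chair once an identical event is reported at least twice within a month, or over six times within half a year.

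**Phase II dose.** The synopsis says "The RPTD will be one dose level lower than the MTD" and Section 10 agrees ("The recommended phase II dose will be 1 dose level below the defined MTD"). The phase II radiation dose item in Section 8, Section 9.2 and Section 9.9 all give the MTD itself.

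**The concern.** Three patients say little about a DLT rate. With 0/3 the one-sided 95% upper bound is 63%, and the protocol reports no earlier clinical study of Sutent with radiation (Section 2c). Because phase II counts the phase I patients at the chosen level towards its 38, up to 38 - 3 = 35 more patients follow a level cleared on 0/3, or 38 - 6 = 32 after 1/6.

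The existing reviews do look at patients and toxicities by dose level, but by judgement. The one numeric trigger counts identical events over calendar time and has no denominator. The DLT definition covers most grade 3-5 non-haematological events and grade 4-5 haematological events. A run of different DLTs, such as pneumonitis in one patient, bleeding in another and hypertension in a third, could reach one third of the cohort without meeting either limb of that trigger. At stake is how early a level that cleared phase I by chance is formally put before the committee.

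**Working it through.** The plan gives no operating characteristics for phase I, so there is no stated figure to reproduce. The range of 3 to 6 patients follows from the rule: 0/3 leaves three, and 1/3 followed by none leaves six. From the protocol come the cohort sizes, the 38 patients, the one-third limit, the 30-day window and accrual of 1-3 a month. The DLT rates and curves are assumptions. Sites are pooled throughout.

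**1. Clearing one level.** Let p be the true DLT rate and q = 1 - p.
- Current rule: q³ + 3pq⁵. At p = 1/3: 0.296 + 0.132 = 0.428.
- Six required, at most 1 DLT: q³(q³ + 3pq²) + 3pq⁵. At p = 1/3: 0.296 × 0.741 + 0.132 = 0.351.
- One-sided 95% upper bounds: 0/3 63.2% (1 - 0.05^(1/3)); 0/6 39.3%; 1/6 58.2%.

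**2. Whole trial.** P(MTD = level k) is the product of the clearing probabilities up to k, times the chance that level k+1 fails. In the columns from the third on, a level that fails at six steps down to the one below; a level 5 that clears goes forward itself under both readings. The last two columns give the chance that a level with a true rate of one third or more goes forward, now → with six required.

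| Assumed curve, levels 1-5 (%) | MTDs resting on 0/3 | Phase II at the MTD | Phase II one level below |
|---|---|---|---|
| 10/20/33/50/60 | 74% | 27% → 23% | 5% → 4% |
| 5/10/20/33/50 | 75% | 27% → 22% | 5% → 4% |
| 5/10/15/20/33 | 75% | 22% → 18% | 22% → 18% |

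**3. Pooled looks after 0/3.** Exact recursion from 0/3 to 38 patients. Trigger if DLTs are at least n/3 at n = 6, 12, 18, 24, 30 or 36. The look at six is the completion step; its rejection probability is 1 - (q³ + 3pq²).

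| True rate | Rejected at six | Referred later | Total |
|---|---|---|---|
| 15% | 6% | 3% | 9% |
| 20% | 10% | 8% | 19% |
| 25% | 16% | 18% | 34% |
| 1/3 | 26% | 39% | 65% |
| 40% | 35% | 50% | 86% |

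(Totals are from unrounded values.) If accrual stopped at every trigger, mean further DLTs after 0/3 would be 6.4 against 35 × 1/3 = 11.7 at one third, and 5.5 against 35 × 0.40 = 14.0 at 40%. With 1 to 4 patients enrolled while the window runs, these become 6.5-6.9 and 5.7-6.3.

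**4. The identical-event trigger.** Over six times within half a year means 7 reports. At 1-3 patients a month that period brings 6 to 18 new patients. The twice-in-a-month limb is much more sensitive, and patients on maintenance Sutent also feed it, but it too needs the same event twice.

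**The case against.** The strongest reply is that nothing here is wrong: the rule is standard, its consequence is stated, and oversight is layered. Most of this stands. A reader might infer that the 3+3 rule is defective; the text does not support that. A reader might also infer that nobody looks at the DLT rate in phase II. Appendix 3 contradicts this, since the regular meetings take up patient numbers and significant toxicities per dose level, and the committee weighs closure. What is absent is a number, not a look.

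It is also fair that the pooled looks lead to a committee that already meets quarterly, so part of the fix makes existing review explicit. The DLT reduction in step 3 is easily read as an expected saving. It is an upper limit, because it starts from 0/3 at a high true rate, treats every referral as a stop, and assumes that no existing review would have acted. If phase II runs one level below the MTD, completing six changes 5% only to 4% on two of the three curves. In that case the chosen level usually has a tolerated level above it, and the step matters mainly for level 5.

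What remains is that DLTs of different kinds have no stated proportion at which referral is compulsory.

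**Conclusion.** The point holds as a minor, low-cost safeguard. The protocol lets the phase II level rest on 0/3, which on the assumed curves is the usual route (74-75% of declared MTDs), and it sets no phase II DLT proportion. Completing six is by itself a modest gain, from 43% to 35% clearance at a true rate of one third. The pooled count adds more, with rejection or referral after 0/3 rising from 26% at six to 65% overall.

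The documents do not support saying that Section 16's one-third limit already binds phase II: it is a phase I limit worded per site, so a limit over all phase II patients would be a new, pooled rule. The two wordings of the phase II dose are a genuine contradiction, but a separate one. It matters here because it decides how much the six-patient step achieves. The sizes rest on assumed DLT rates, pooling over sites and independent patients.

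**What to change.** 1. **Complete six.** Require six patients observed for the 30-day DLT window, with at most 1 DLT, at the level taken forward. If only three were treated, the first three phase II patients complete the six and count towards the 38. If 2 or more of six have a DLT, complete the next lower level in the same way. If level 1 fails, stop and refer to the committee.
2. **Set referral points.** In phase II, apply Section 16's DLT definition and window to all patients. State that this is a pooled extension of the per-site limit and separate from the Section 9.10 list that governs individual Sutent changes. If DLTs reach one third or more at 12, 18, 24, 30 or 36 patients, refer accrual to the Clinical Trials Monitoring Committee, which decides. Leave the identical-event trigger as it is.
3. **Choose one phase II dose.** The sponsor should use a single wording in the synopsis and Sections 8, 9.2, 9.9 and 10.

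**Cost.** A short amendment. If the level holds, no patients are added and phase II waits about one extra 30-day period. If it fails at six, those six do not count towards the 38, and enrolment rises by 3 + 35 - 35 = 3 or 3 + 32 - 35 = 0, depending on whether the lower level already has three or six patients. The main downside is alarms at rates below the limit: rejection or referral in 9%, 19% and 34% of trials at 15%, 20% and 25%. Later referrals at those rates come on average at 15 to 18 patients, who would be lost to the 38 if the committee closed the level. Six patients are 2 to 6 months of accrual, so the looks fall near the committee's quarterly meetings.

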**Statistical analysis:**

*Phase I: Feasibility and toxicity.* Patients will receive concurrent treatment with extracranial radiosurgery and Sutent. Both the radiation dose and Sutent dose will be escalated as the trial progresses from Levels 1 through 5 as shown in Table 1. The starting radiation dose is 40 Gy in 10 fractions and the starting Sutent dose is 25 mg PO QD. The dose escalation strategy is as follows: The trial will start with dose level 1. At each level, 3 patients will be treated and their toxicities will be assessed. If no patients experience dose limiting toxicity, the trial will proceed to the next dose level. If 1 patient develops unexpected acute toxicity at any dose level, an additional 3 patients will be treated at that dose level. If ≥2 patients experience unexpected toxicity, the previous dose level will be declared the maximal tolerated dose for Phase II evaluation

*Phase II (Includes 3 to 6 patients from Phase I MTD):* The median progression free survival with optimal chemotherapy alone for the 4 most common tumor types (lung, breast, prostate and colorectal) ranges from 2.2 to 10.6 months, depending on primary tumor site and degree of pretreatment. Therefore, we will assume a median time to progression of 6.4 months (standard deviation 3.2 months) with chemotherapy alone. Using the data from this trial, response rates will be estimated and Kaplan-Meier curves generated for progression-free and overall survival (1). With 38 patients for the phase II portion, this study has 87% power (α=0.05) to detect a 25% increase in time to progression. Also the 2 year freedom from progression is <5% with chemotherapy therapy and this study has 70% power (α=0.05) to demonstrate a 10% absolute increase in 2 year progression-free survival.

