**Phase I Dose Levels**

| **Dose Level** | **Radiation Dose** | **Sutent Dose** |
| --- | --- | --- |
| 1 | 40 Gy in 10 fractions | 25 mg PO QD |
| 2 | 40 Gy in 10 fractions | 37.5 mg PO QD |
| 3 | 50 Gy in 10 fractions | 37.5 mg PO QD |
| 4 | 50 Gy in 10 fractions | 50 mg PO QD |
| 5 | 60 Gy in 10 fractions | 50 mg PO QD |

1. Radiation Doses (Phase II): The radiation dose used in the MTD dose level will be used throughout the phase II portion of this study.
2. Dose/volume constraints: The dose distribution will be converted to the normalized isoeffective dose, equivalent to dose given at standard fractionation (2 Gy per fraction). Normal tissue tolerance doses to be used as guidelines for treatment plan evaluation are: (based on the treatment on the sum of all involved sites):
3. Spinal cord:
   - 1. Must keep each dose < 300 cGy/fraction (therefore maximum total spinal cord dose will be 3000 cGy)
     2. Same segment of spinal cord must not be in more than 1 treatment field
   1. Skin: Maximum skin dose 40 Gy
   2. Lung: Volume receiving > 20 Gy less than 30%
   3. Liver: Volume receiving > 30 Gy less than 50%
   4. Kidney: Volume receiving > 20 Gy (both kidneys) should be less than 50%
   5. Esophagus: Maximum esophageal dose ≤ 40 Gy
   6. Heart: Volume >25 Gy less than 60% and maximum heart dose <30 Gy
   7. Major Vessels: Maximum dose 40 Gy
   8. Bone marrow: Must limit the radiation to < 30% of bone marrow

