**9. DRUG THERAPY - SUTENT**

9.1 Phase I Dose (days 1-28):

| **Dose Level** | **Radiation Dose** | **Sutent Dose** |
| --- | --- | --- |
| 1 | 40 Gy in 10 fractions | 25 mg PO QD |
| 2 | 40 Gy in 10 fractions | 37.5 mg PO QD |
| 3 | 50 Gy in 10 fractions | 37.5 mg PO QD |
| 4 | 50 Gy in 10 fractions | 50 mg PO QD |
| 5 | 60 Gy in 10 fractions | 50 mg PO QD |

9.2 Phase II Dose (days 1-28): Phase II will be the MTD from Phase I

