**Phase II dose level will be MTD determined by Phase I**

**↓**

Additional chemotherapy (as determined by Medical Oncology)

**↓**

Maintenance Sutent (until death or progression) and appropriate follow-up

- Two weeks after completion of any chemotherapy, maintenance Sutent in 6 week cycles (consisting of Sutent 50 mg PO QD weeks 1-4 followed by no treatment weeks 5-6) until progression or death

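### The protocol sets the phase II dose both at the MTD and one level below it, so a failure at dose level 3, 4 or 5 gives two different doses and a failure at level 2 leaves one rule with none

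*Protocol*

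**What the plan says.** **Phase II at the MTD, with the MTD being the level below the failing one.**

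- Section 10, stopping rule: with two or more DLTs among three patients, "dose escalation will be terminated and the next lowest dose level will be declared the maximal tolerated dose for Phase II evaluation".
- Synopsis, Statistical analysis: "the previous dose level will be declared the maximal tolerated dose for Phase II evaluation".
- Section 8.1, phase II radiation dose: "The radiation dose used in the MTD dose level will be used throughout the phase II portion of this study".
- Section 9.2: "Phase II will be the MTD from Phase I".
- Section 9.9: "Phase II dose level will be MTD determined by Phase I".
- Section 16 treats a level with two or more DLTs in six patients as exceeding the MTD and recommends the level directly beneath it. Section 16 and the synopsis also count the 3 to 6 phase I patients treated at the MTD in the phase II sample.

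**Phase II one level below the MTD.**

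- Section 10, last bullet: "The recommended phase II dose will be 1 dose level below the defined MTD", or the highest dose tested if the MTD was not reached.
- Synopsis, Treatment Plan: "The RPTD will be one dose level lower than the MTD", followed by "If the MTD is not reached at dose level 5, no further escalation will occur and this will be the RPTD".

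Section 1 makes the recommended phase II dose (RPTD) a phase I primary objective and states the phase II primary objectives for patients treated at the RPTD. The RPTD and the phase II dose are therefore the same quantity.

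**The concern.** Two current rules answer one question: which dose do phase II patients receive? The first stops at the tolerated level. The second takes that level, already one step below the failure, and steps down again. Section 10, which governs escalation, contains both.

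At stake are a phase I primary objective and the regimen on which phase II progression-free and overall survival are to be reported. Two investigators following the text faithfully could treat the phase II cohort at different radiation or Sutent doses. In one outcome, the second rule gives no dose at all.

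**Working it through.** The protocol states no figure to reproduce here, so the check is to run both rules through every outcome and then ask how often they part.

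**Step 1. Doses under each rule.** Let f be the failing level. The MTD rule gives level f − 1. The MTD-minus-one rule gives level f − 2. Doses come from the phase I dose-level table in Section 10.

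| Outcome | MTD rule | MTD-minus-one rule | Difference |
| --- | --- | --- | --- |
| Level 5 fails | Level 4: 50 Gy / 50 mg | Level 3: 50 Gy / 37.5 mg | 12.5 mg |
| Level 4 fails | Level 3: 50 Gy / 37.5 mg | Level 2: 40 Gy / 37.5 mg | 10 Gy |
| Level 3 fails | Level 2: 40 Gy / 37.5 mg | Level 1: 40 Gy / 25 mg | 12.5 mg |
| Level 2 fails | Level 1: 40 Gy / 25 mg | none defined | no dose |
| None fails | Level 5: 60 Gy / 50 mg | Level 5: 60 Gy / 50 mg | none |

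If level 1 fails, neither rule names a level. That outcome is not part of this point.

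**Step 2. How often the rules part.** The protocol gives no DLT rate, so the rates p below are assumptions. Under 3+3, a level is cleared with 0 of 3 DLTs, or with 1 of 3 followed by 0 of 3:

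q(p) = (1 − p)³ + 3p(1 − p)⁵

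With the same p at every level:

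- two different existing doses (level 3, 4 or 5 fails) = q² − q⁵
- no dose under the second rule (level 2 fails) = q(1 − q)
- rules agree (all five clear) = q⁵
- level 1 fails = 1 − q

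| Assumed p | q | Two doses | No dose under second rule | All clear | Level 1 fails |
| --- | --- | --- | --- | --- | --- |
| 0.10 | 0.906 | 0.210 | 0.085 | 0.611 | 0.094 |
| 0.15 | 0.814 | 0.305 | 0.152 | 0.357 | 0.186 |
| 0.20 | 0.709 | 0.323 | 0.206 | 0.179 | 0.291 |

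With assumed rates rising over levels 1 to 5 as 0.05, 0.10, 0.15, 0.20, 0.25, q is 0.973, 0.906, 0.814, 0.709, 0.600. Then:

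- level 3 fails: 0.973 × 0.906 × (1 − 0.814) = 0.164
- level 4 fails: 0.973 × 0.906 × 0.814 × (1 − 0.709) = 0.209
- level 5 fails: 0.973 × 0.906 × 0.814 × 0.709 × (1 − 0.600) = 0.204
- two different doses in total: 0.577
- level 2 fails: 0.973 × (1 − 0.906) = 0.091
- all clear: 0.305

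(Results use unrounded q.)

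**Step 3. Sample size, power and pooling.** Neither rule enters the 38 patients or the 87% power. Under the MTD-minus-one rule, if level 5, 4 or 3 fails, the resulting level 3, 2 or 1 was itself cleared with 3 patients (0 of 3) or 6 patients (1 of 6). So 3 to 6 phase I patients would still be available to pool, but they would be those treated at the RPTD, not those at the MTD named in Section 16.

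**The case against.** The strongest reply is that the two outlying sentences use MTD loosely for the level that fails. Both speak of the MTD being reached, or not, by escalation. One level below the failing level is f − 1, which is what every other section gives. On that reading there is one dose for each outcome, the missing dose after a level 2 failure disappears, and the fault is only a term used in two senses.

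That is plausible, and it is probably what was meant. It does not rescue the text. The bullet in Section 10 refers to the MTD as defined, and the only definition in that section is the tolerated level. If the failing-level sense were carried through instead, Sections 8.1, 9.2 and 9.9 would put phase II patients on the dose that had just failed. The protocol is consistent only if the term changes meaning between sentences without notice, and in a rule that assigns doses that is a defect.

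Three further points stand. The percentages are the chance that a relevant level fails, not the chance that anyone receives an unintended dose, and a flat rate is a crude model for rising doses. The calculation uses one 3+3 for the whole trial, although Sections 10 and 16 contain some site-specific wording. And where the literal rules differ, the second gives the lower dose, so applying it would not take patients above the tolerated level.

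**Conclusion.** The point holds: the dose-assignment text is wrong as written and should be corrected. A failure at level 3, 4 or 5 yields two doses, 12.5 mg of Sutent or 10 Gy apart. A failure at level 2 yields no dose under one rule. The rules agree if no level fails.

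This conclusion rests on the wording alone. The frequencies are illustrative: 21%, 31% and 32% for two different doses, and 9%, 15% and 21% for no dose, at assumed flat DLT rates of 10%, 15% and 20%; 58% and 9% under the assumed rise from 5% to 25%. Most sections point to the MTD rule, so the likely intent can be recovered.

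**What to change.** Amend two sentences, the RPTD sentence in the synopsis Treatment Plan and the last bullet of Section 10, to state that the RPTD is the MTD, meaning the level immediately below the failing level, or level 5 if none fails. This agrees with the synopsis statistical paragraph and Sections 8.1, 9.2, 9.9 and 16. Sample size, pooling and power do not change.

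If one level below the MTD is truly intended, correct the synopsis statistical paragraph, Sections 8.1, 9.2 and 9.9, the stopping rule in Section 10, and Section 16 instead. State the phase II dose when the MTD is level 1, and pool the phase I patients treated at the RPTD rather than at the MTD. This takes more rewording, but the sample size and power again need not change.
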